**ABBREVIATIONS AND DEFINITIONS**

AIDS – Acquired Immunodeficiency Syndrome  
 BRST – Behavioral Risk Screening Tool  
 CDC – Centers for Disease Control and Prevention  
 CDPHE – Colorado Department of Public Health and Environment  
 CER – Cost-Effectiveness Ratio  
 CHIP – Children’s Hospital Colorado Immunodeficiency Program  
 CI – Confidence Interval  
 COMIRB – Colorado Multiple Institutional Review Board  
 DHMC – Denver Health Medical Center  
 DHRS – Denver HIV Risk Score  
 ED – Emergency Department  
 EDWIN – Emergency Department Work Index  
 HAART – Highly Active Antiretroviral Therapy  
 HIV – Human Immunodeficiency Virus  
 ICER – Incremental Cost-Effectiveness Ratio  
 ILHE – Individual Level Health Education  
 IQR – Interquartile Range  
 IRB – Institutional Review Board  
 MSM – Men Who Have Sex with Men  
 PCM – Prevention Case Management  
 RR – Risk Ratio  
 SD – Standard Deviation  
 SFTP – Secure File Transfer Protocol  
 UCH – University of Colorado Hospital  
 USPSTF – United States Preventive Services Task Force  
 WHO – World Health Organization

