## 4. METHODS

### A. Study Design

#### Specific Aim 1

For this aim, we will perform a multi-center, prospective, randomized, controlled clinical trial to evaluate the effectiveness of three distinct HIV screening approaches. Implementation of a randomized controlled trial will incorporate use of “pragmatic” or effectiveness methodologies, and will allow us to compare

[figure not shown]

the effectiveness of the three screening approaches while minimizing threats to internal validity. Patients will be screened using one of three interventions in a 1:1:1 random sequence; patients will therefore be offered HIV testing based on the results of which screening arm they are assigned, and in the case of the two screening tools, the results of risk assessment. All screening methodologies will be integrated into electronic patient triage systems at each site; as such, the actual randomization process will also be integrated into the electronic system, allowing for real-time concealed random allocation (**Figure 1**). Nurses who perform screening and all ED staff (e.g., physicians, nurses, and technicians) will understand the conceptual goals of the project but will be blinded to the specific hypotheses, and patients will be completely blinded to the purpose of the study.

All of the participating sites have established ED-based HIV testing programs, and all of the testing procedures that occur after patients are identified for HIV testing (i.e., consent for the test, performance of the test, results disclosure, linkage to care, etc.) will have been integrated into clinical processes within each ED as standards of care. The specific interventions being evaluated in this

study relate only to how patients are identified for and offered HIV testing. The standard process used by the DHMC ED and the integration of the three study interventions is described by the “ED Rapid HIV Screening Workflow” figure (**Appendix**).

#### Specific Aims 2 and 3

For these aims, we will perform prospective cohort studies nested in the clinical trial described above.

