All cost and time-motion data will be manually entered and analyses will be performed using Microsoft Excel (Microsoft Corporation, Redmond, WA). Double data entry will be performed to minimize data entry error. Total direct costs will be calculated and compared between interventions. As each intervention will not extend beyond 12-months, it will be unnecessary to discount costs, although all costs will be annualized. We will use the number of newly-diagnosed HIV-infected patients, the primary outcome from Specific Aim 1, as an intermediate outcome for this aim. The scope of this aim is not to perform decision analyses or disease transition-state modeling, but instead to systematically collect valid cost data and to report cost effectiveness of the 3 screening approaches using an intermediate outcome. Results of this aim will inform future modeling, including from a society perspective, by our team. Total direct costs per patient identified with HIV infection at the institutional level will be reported as CERs and incremental CERs, or the additional costs per patient identified with HIV infection beyond those incurred by nontargeted screening. Because underlying distributions of cost data are often skewed, we will report bootstrap 95% CIs for each CER and ICER. Finally, sensitivity analyses will be performed to determine the effects of individual parameter ranges on the results.

### Specific Aim 3

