## **I. Sample Size Estimation**

The primary hypothesis of this study is that enhanced targeted HIV screening will be significantly associated with new HIV diagnoses when compared to nontargeted HIV screening. As described above, the primary statistical measure will include an unadjusted RR. Based on our *a priori* assumptions related to the performance of each screening method weighted across the four study sites (i.e., nontargeted screening – 25% HIV test completion, 0.3% HIV test prevalence; enhanced targeted screening – 5% HIV test completion, 2% HIV test prevalence), we anticipate requiring a minimum of 12,600 HIV tests performed to achieve a statistically significant association using an alpha of 0.05 (i.e., estimated unadjusted RR = 1.33, 95% CI: 1.01-1.79). We also anticipate adjusting variance estimates to account for within-institution correlation; as such, we will plan to complete at additional 10%, resulting in a total of 14,000 HIV tests performed.

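### The protocol defines the incremental cost-effectiveness ratio without an incremental denominator, so the wording as it stands does not give additional cost per additional diagnosis

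*Protocol*

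**What the plan says.** Section 4.H, Analytic Plan, Specific Aim 2, sets the effect measure: "We will use the number of newly-diagnosed HIV-infected patients, the primary outcome from Specific Aim 1, as an intermediate outcome for this aim". The cost per patient found is then to be reported in two forms, as average cost-effectiveness ratios (CERs) and as "incremental CERs, or the additional costs per patient identified with HIV infection beyond those incurred by nontargeted screening". Each CER and each ICER is to carry a bootstrap 95% confidence interval.

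The list of abbreviations has "ICER – Incremental Cost-Effectiveness Ratio", which gives the name but no formula. Section 4.F, Outcome Measures, Specific Aim 2, lists total programme costs, cost per person tested and cost per case detected, compared by arm, and does not mention an incremental ratio. So the sentence in section 4.H is the only definition in the protocol.

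**The concern.** The sentence in section 4.H uses one denominator, patients identified, for both the average and the incremental ratio. What is taken beyond nontargeted screening is cost alone. Nothing says that the denominator is the additional patients found.

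Dividing extra cost by all patients identified credits the extra spending with diagnoses that nontargeted screening would also have made. If a targeted arm costs more and finds more, the cost of each extra diagnosis is then understated. The bootstrap interval would be built around the same misdefined quantity, and section 4.H expects the Aim 2 results to inform later modelling.

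The wording also gives a finite number where an ICER should not be quoted. Section 3, Preliminary Studies, reports that in the single-centre pilot both methods found the same number of new diagnoses, with fewer tests under the risk score. If the trial repeats that result, the difference in diagnoses is zero and the ICER is undefined. The written rule would still return a value.

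**Working it through.** **Inputs**

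- Nontargeted arm, section 4.I: "nontargeted screening – 25% HIV test completion, 0.3% HIV test prevalence".
- Enhanced targeted arm, section 4.I: "enhanced targeted screening – 5% HIV test completion, 2% HIV test prevalence".
- Allocation, section 4.A: "Patients will be screened using one of three interventions in a 1:1:1 random sequence". The arms therefore have equal numbers of visits in expectation, and counts can be compared directly.
- Costs: none are given in the protocol. They are kept as symbols, or as assumed multiples of the nontargeted cost.

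**Step 1: reproduce the plan's own figure.** Yield per visit is test completion times test prevalence.

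- Nontargeted: 0.25 × 0.003 = 0.00075, so E_N = 0.75 per 1,000 visits.
- Enhanced: 0.05 × 0.02 = 0.00100, so E_E = 1.00 per 1,000 visits.
- Risk ratio: 1.00/0.75 = 1.333, which agrees with the point value in "estimated unadjusted RR = 1.33, 95% CI: 1.01-1.79".

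**Step 2: three candidate quantities.** Let C_E and C_N be the total direct costs per 1,000 visits.

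- Standard ICER: (C_E − C_N)/(E_E − E_N) = (C_E − C_N)/0.25.
- Literal reading: (C_E − C_N)/E_E = (C_E − C_N)/1.00.
- Difference of average ratios: C_E/E_E − C_N/E_N = C_E/1.00 − C_N/0.75.

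**Step 3: the literal reading against the ICER.** The ratio is (E_E − E_N)/E_E = 0.25/1.00 = 0.25 whenever the costs differ. With equal arms it equals 1 − 1/RR, so it moves with the risk ratio. Taking the two limits in section 4.I merely as other values of RR, it is 1 − 1/1.01 = 0.01 and 1 − 1/1.79 = 0.44.

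**Step 4: the difference of CERs against the ICER.** Set C_N = 1 and vary C_E; these multiples are assumptions. For example, at C_E = 1.1 the ICER is 0.1/0.25 = 0.40, the literal value is 0.1/1.00 = 0.10, and the difference of CERs is 1.100 − 1.333 = −0.233.

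| C_E (C_N = 1) | ICER | Literal | Literal/ICER | CER difference | CER difference/ICER |
|---|---|---|---|---|---|
| 0.50 | −2.00 | −0.50 | 0.25 | −0.83 | 0.42 |
| 0.75 | −1.00 | −0.25 | 0.25 | −0.58 | 0.58 |
| 1.10 | 0.40 | 0.10 | 0.25 | −0.23 | −0.58 |
| 1.50 | 2.00 | 0.50 | 0.25 | 0.17 | 0.08 |
| 2.00 | 4.00 | 1.00 | 0.25 | 0.67 | 0.17 |
| 5.00 | 16.00 | 4.00 | 0.25 | 3.67 | 0.23 |

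The difference of CERs is negative whenever C_E/C_N is below 1.333. Between cost ratios of 1 and 1.333, the enhanced arm costs more and finds more, so the ICER is positive, yet the difference of CERs is negative and would look like a saving.

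In the first two rows the enhanced arm costs less and finds more. That is dominance, and the size of a negative ratio there has no useful meaning under any definition.

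**Step 5: the traditional targeted arm.** The same formulas apply, but section 4.I gives no yield for this arm, so no factor can be calculated. If it found fewer cases than nontargeted screening, E_T − E_N would be negative and the literal value would have the opposite sign to the ICER.

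**The case against.** The strongest reply is that this is loose prose around a standard term. Section 4.H names the incremental ratio, the abbreviation list expands it in the usual way, and no numerator or denominator is written as a formula. A trained analyst would probably compute the standard ICER, and a statistical analysis plan, which is not at hand, may spell it out. Total costs by arm and absolute numbers of new diagnoses are both to be reported, so a reader could form the correct ratio from them. These arguments stand as reasons to rate the point low. They do not make the definition right: the protocol does not leave the matter to a later document but states a definition, and it does not match the term.

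Three stronger inferences are tempting, and the documents do not support them.

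- A reader might infer that the trial will report one quarter of the true ICER. That factor belongs to one of two possible readings and to one of the two targeted arms.
- A reader might infer that the result for Hypothesis 2 is at risk. That hypothesis is framed as cost per newly identified patient, and section 4.F lists cost per case detected; both point to the average CER. The ICER is an added report.
- A reader might infer that the cost of targeted screening will certainly be understated. That needs a targeted arm that costs more and finds more. The protocol gives no costs, and a cheaper targeted arm is compatible with Hypothesis 2 and with the smaller number of tests in the pilot.

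**Conclusion.** The point holds as a minor correction to a secondary-aim estimate. Neither reading of the definition in section 4.H gives the difference in cost over the difference in new diagnoses.

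On the literal reading the value is 0.25 of the ICER for enhanced versus nontargeted screening. This assumes the section 4.I yields and equal arms, and is an illustration, not a forecast. On the difference-of-CERs reading no single factor applies; over the assumed cost multiples shown, the ratio to the ICER runs from −0.58 to 0.58. No figure can be given for the traditional targeted arm.

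No design feature, data item or Aim 1 analysis is affected.

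**What to change.** In section 4.H, Specific Aim 2, replace the definition with wording such as: the incremental CER is the total direct cost of the targeted arm minus that of the nontargeted arm, divided by the number of new diagnoses in the targeted arm minus the number in the nontargeted arm, that is, the additional cost per additional new diagnosis. Add that where one arm costs less and finds at least as many new cases, dominance is reported instead of a ratio. Keep the average CERs as a separate line, and carry the same definition into any statistical analysis plan.

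The cost is a sentence or two of text. It needs no new data and no change to the sample size or to data collection.

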### **Specific Aim 2: To measure and compare programmatic costs associated with implementation of targeted and nontargeted rapid HIV screening strategies when fully-integrated into ED settings**

**Hypothesis 2:** Enhanced and traditional targeted rapid HIV screening is more cost effective per newly-identified HIV-infected patient than nontargeted rapid HIV screening from the institutional perspective.

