## **F. Outcome Measures**

### Specific Aim 1

Confirmed newly-diagnosed HIV infection will serve as our primary outcome. In anticipation of testing patients with previously diagnosed HIV infection (i.e., repeat diagnoses), our secondary outcome will include a composite of new diagnoses and repeat diagnoses.

Although confirmed newly-diagnosed HIV infection will serve as the primary outcome for this study, we believe important secondary effectiveness evaluations include disease state at the time of diagnosis as well as a longer-term evaluation of access to care, disease progression, and treatment. Therefore, additional outcomes will include behavioral risk information, CD4 count (cells/ $\mu$ L) and viral load (copies/mL) at the time of diagnosis, and successful linkage into care (defined as completion of an initial HIV clinic visit). Details of follow-up care and disease progression for a period of one year following diagnosis will also be collected, including the number of scheduled and unscheduled medical care visits, whether antiretroviral therapy and treatment for opportunistic infections were initiated, the number of hospitalizations, and mortality.

### Specific Aim 2

Programmatic costs associated with implementation of targeted and nontargeted rapid HIV screening strategies when fully-integrated into ED settings will be measured. We will estimate program costs using a simple cost allocation method that sums fixed and variable costs for program implementation. Components of costs by intervention arm will include: start-up, personnel, tests, supplies, and equipment. In order to estimate personnel-related costs by arm, time-motion data will be collected during randomly-selected time periods of the trial at each site (including different times of day and weekends). Personnel time spent per patient will be monetized by position title-specific median salary data from the Bureau of Labor Statistics for the respective metropolitan statistical area. Total programmatic costs, costs per person tested, and cost per HIV case detected will be compared by intervention arm. Differences across sites will be explored in sensitivity analyses. Uncertainty in cost estimates will be estimated using bootstrapping resampling methods.

### Specific Aim 3

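### Aim 2 takes every incremental cost-effectiveness ratio against nontargeted screening, so no incremental ratio between the two targeted arms is planned, and the planned ratios may be negative and unable to rank the strategies

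*Protocol*

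**What the plan says.** Aim 2 sets out to "report cost effectiveness of the 3 screening approaches using an intermediate outcome" (Protocol 4.H, Specific Aim 2). The same paragraph defines the incremental measure as "incremental CERs, or the additional costs per patient identified with HIV infection beyond those incurred by nontargeted screening" and adds that "we will report bootstrap 95% CIs for each CER and ICER". The definition matches Hypothesis 2 in section 1: "Enhanced and traditional targeted rapid HIV screening is more cost effective per newly-identified HIV-infected patient than nontargeted rapid HIV screening from the institutional perspective".

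Other sentences compare all three arms without using increments. Section 4.H states: "Total direct costs will be calculated and compared between interventions". Section 4.F states: "Total programmatic costs, costs per person tested, and cost per HIV case detected will be compared by intervention arm". The Aim 1 analysis in 4.H also compares absolute numbers of new diagnoses. Section 4.H limits the aim: "The scope of this aim is not to perform decision analyses or disease transition-state modeling".

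The protocol names no incremental ratio for enhanced versus traditional screening and no step for identifying dominated strategies.

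**The concern.** The three arms are alternatives, and a hospital would adopt one of them. For that choice an increment is normally taken against the next cheaper strategy that is not dominated. The protocol fixes one reference arm for both increments, and on its own test rates that arm is unlikely to be the cheapest.

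Two things follow. First, if a targeted arm costs less and finds more than nontargeted screening, its ratio is negative. A negative ratio becomes larger in size when the saving grows, but also when the gain in diagnoses shrinks, so two such ratios cannot be ordered. Second, if the dearer targeted arm finds more infections than the cheaper one, the cost of each extra diagnosis is the figure a hospital needs, and no planned ratio or interval gives it. Hypothesis 3 compares enhanced directly with traditional screening on ED operations, so the protocol itself treats that contrast as relevant.

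**Working it through.** **Inputs from the protocol.** Section 4.I: nontargeted 25% test completion and 0.3% test prevalence; enhanced 5% and 2%. Section 4.D: 1:1:1 allocation. Sections 4.I and 5.C: 14,000 tests and up to 120,000 subjects. No unit costs and no traditional-arm rates are given.

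**Reproducing the plan's figure.** New diagnoses per visit: 0.25 × 0.003 = 0.00075 and 0.05 × 0.02 = 0.00100. The ratio is 0.00100 / 0.00075 = 1.33, the risk ratio in section 4.I. The protocol gives no cost or incremental-ratio figure to reproduce.

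**Tests and diagnoses per 10,000 visits.** Nontargeted: 2,500 tests, 7.5 diagnoses. Enhanced: 500 tests, 10 diagnoses. That is five times the tests for fewer diagnoses.

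**When nontargeted is dearer than enhanced.** Let t be the cost of a completed test and q the cost of one risk assessment. On variable costs alone the condition is 0.25t > 0.05t + q, so q < 0.20t. For assumed t of USD 20, 40 or 60, the limit on q is USD 4, 8 or 12.

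**Traditional completion.** The rate implied by 14,000 tests is 14,000 / (N/3) − 0.25 − 0.05, where N is the total number of subjects:

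| N | Implied completion |
|---|---|
| 120,000 | 5% |
| 100,000 | 12% |
| 90,000 | 16.7% |
| about 76,400 | 25% |

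Since 120,000 is a ceiling, 5% is the low end.

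**Illustration 1: negative ratios cannot rank.** Assumed: 40,000 visits per arm, t = USD 40, q = USD 2, traditional completion 10% and prevalence 0.85%.

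| Arm | Cost (USD) | Diagnoses | Cost per diagnosis | Planned increment vs nontargeted |
|---|---|---|---|---|
| Nontargeted | 10,000 × 40 = 400,000 | 30 | 13,333 | – |
| Enhanced | 2,000 × 40 + 40,000 × 2 = 160,000 | 40 | 4,000 | −240,000 / 10 = −24,000 |
| Traditional | 4,000 × 40 + 40,000 × 2 = 240,000 | 34 | 7,059 | −160,000 / 4 = −40,000 |

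Traditional has the more negative ratio, yet enhanced costs USD 80,000 less and finds 6 more. The same reversal occurs in all nine combinations of t = USD 20, 40 or 60 with q = USD 0, 1 or 2. The average cost per diagnosis ranks enhanced first.

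**Illustration 2: the unreported increment.** Assumed: per 10,000 visits, t = USD 30, q = USD 1, traditional completion 12% and prevalence 0.9%.

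| Arm | Cost (USD) | Diagnoses | Cost per diagnosis |
|---|---|---|---|
| Enhanced | 500 × 30 + 10,000 = 25,000 | 10 | 2,500 |
| Traditional | 1,200 × 30 + 10,000 = 46,000 | 10.8 | 4,259 |
| Nontargeted | 2,500 × 30 = 75,000 | 7.5 | 10,000 |

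Both targeted arms dominate nontargeted. Traditional versus enhanced: (46,000 − 25,000) / (10.8 − 10) = USD 26,250 per additional diagnosis.

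With a common q, the cost difference is 700t, so the increment is USD 17,500 at t = 20 and USD 35,000 at t = 40. At t = 30 it is 21,000 / 2 = USD 10,500 if traditional prevalence is 1.0% (12 diagnoses), and 21,000 / 0.2 = USD 105,000 if it is 0.85% (10.2 diagnoses). Below 10 / 1,200 = 0.83%, enhanced dominates traditional.

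**Equal diagnoses.** Section 3, item 3 reports a pilot in which the risk score and nontargeted screening found equal numbers of new diagnoses. With that result the planned denominator is zero and the ratio is undefined.

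**The case against.** The case for leaving the text alone has four parts.

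- *The arms are compared.* A reader might infer that the two targeted arms are never compared, or that a dominated strategy would pass unnoticed as cost effective. The protocol does not support either reading. Sections 4.F and 4.H compare total costs, cost per case and diagnoses across all arms. A dominated arm always has a higher average cost per diagnosis than the arm that dominates it, so simple dominance would be seen. This stands. The point estimate of the missing increment can also be worked out from reported totals and counts, but its bootstrap interval cannot.
- *The cost order is unknown.* A reader might infer from the test rates that nontargeted screening is the costliest arm. The rates establish only more tests than enhanced. The targeted arms carry questionnaire time at every visit and programming costs, and at 25% completion traditional screening would match nontargeted on tests and add the questions. This stands; the cost order is an assumption.
- *The reference arm fits the hypothesis.* Hypothesis 2 asks about each targeted strategy against nontargeted screening, which section 4.D describes as the currently recommended approach. This is a good reason to keep those comparisons. It does not make them sufficient for an aim that covers three approaches.
- *Scope and detail.* Decision analysis is disclaimed, and rules on dominance could sit in an analysis plan not shown here. But the protocol already commits to incremental ratios and fixes their comparator. Ordering three observed arms by cost and subtracting needs no decision model.

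**Conclusion.** The point holds in a limited form. The protocol states one comparator for all incremental ratios, and so plans no ratio or interval between the targeted arms. If nontargeted screening costs more than enhanced, the section 4.I rates make the planned enhanced ratio negative, and such ratios cannot be ranked by size.

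The five-fold difference in tests and the 7.5 versus 10 diagnoses per 10,000 visits come from the protocol. The USD 26,250 increment, and its range of USD 10,500 to 105,000 over traditional prevalences of 1.0% to 0.85%, rest on assumed unit costs and traditional-arm rates. They show what could be hidden and predict nothing. It would go too far to conclude that Aim 2 cannot inform a choice among the arms: the planned totals, counts and average ratios already carry much of the information. The gap is the incremental price between the targeted arms and its uncertainty. It does not touch the trial's primary analysis.

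**What to change.** In section 4.H, Specific Aim 2, replace the definition of the incremental ratio with this rule:

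- Order the three strategies by total cost and identify any that is dominated or extendedly dominated.
- Report each remaining strategy's increment against the next cheaper remaining one.
- Whatever the ordering shows, report the enhanced-versus-traditional difference in cost and difference in diagnoses, each with a bootstrap 95% interval.
- Label a negative ratio as dominant or dominated, and do not rank negative ratios by size.
- Keep the comparisons of each targeted arm with nontargeted screening as the answer to Hypothesis 2.

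The cost is a few sentences and a small amount of extra analysis on data already being collected.

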- 3) The use of an empirically-derived, externally-validated risk-based instrument, the Denver HIV Risk Score (DHRS), accurately categorizes patients into groups with increasing probability of HIV infection, and when implemented in an urban ED setting is associated with new HIV diagnoses when compared to nontargeted screening. In a single-center pilot comparison of the DHRS to nontargeted screening, we found that while both HIV screening methods identified the same absolute number of newly-diagnosed patients, significantly fewer tests were required when using the DHRS to target patients for screening. The DHRS was refined further and externally validated using a national HIV testing cohort. In this study two items related to specific sexual behavior (receptive anal intercourse and

vaginal intercourse) were removed in order to create a more succinct and easier to implement risk assessment tool. This refined DHRS performed similarly to the original DHRS.

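### The bootstrap 95% CI planned for the ICER has a denominator whose own 95% interval includes zero at the planned size, so the ratio interval would mix results with opposite meanings

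*Protocol*

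**What the plan says.** Protocol section 4.H, Specific Aim 2, sets the effect measure: "We will use the number of newly-diagnosed HIV-infected patients, the primary outcome from Specific Aim 1, as an intermediate outcome for this aim". It reports a cost-effectiveness ratio (CER) for each approach and "incremental CERs, or the additional costs per patient identified with HIV infection beyond those incurred by nontargeted screening". It then adds "we will report bootstrap 95% CIs for each CER and ICER", giving skewed cost data as the reason. It does not say what is reported if one arm is both cheaper and finds more cases, or if replicates fall on both sides of a zero difference in diagnoses.

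Section 4.I gives the planning rates: nontargeted "25% HIV test completion, 0.3% HIV test prevalence"; enhanced targeted "5% HIV test completion, 2% HIV test prevalence"; and the expected result, "estimated unadjusted RR = 1.33, 95% CI: 1.01-1.79". Section 5.C allows up to 120,000 subjects in all, and section 4.D sets 1:1:1 allocation. Section 3 says of the single-center pilot that "both HIV screening methods identified the same absolute number of newly-diagnosed patients", with fewer tests under the risk score.

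**The concern.** The reason given for bootstrapping concerns the numerator (skewed costs). The difficulty lies in the denominator, a difference between two small counts of diagnoses. When replicates of that difference fall on both sides of zero, the sign of the ratio stops identifying the result:

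- A positive ratio can mean costlier and finds more, or cheaper and finds fewer.
- A negative ratio can mean cheaper and finds more (dominant), or costlier and finds fewer (dominated).
- Near zero difference the ratio becomes very large in either direction, and at zero it is undefined.

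Ordering such values and taking the 2.5th and 97.5th percentiles does not give an interval with a cost-per-extra-diagnosis reading. The incremental ratio is one of the two ratio results of Aim 2, and section 4.H intends the aim's results to feed later modeling.

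**Working it through.** **Inputs.** Section 4.I: nontargeted 25% completion and 0.3% prevalence; enhanced 5% and 2%. Section 5.C: up to 120,000 subjects, so 120,000/3 = 40,000 visits per arm. The Protocol gives no cost amounts, so costs below are in units of one test and the extra cost of risk assessment per targeted visit is varied. Visits are treated as independent.

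**The plan's own figure first.**
- Diagnoses per visit: 0.25 × 0.003 = 0.075% and 0.05 × 0.02 = 0.100%. RR = 0.100/0.075 = 1.33, which reproduces. The inflation also reproduces: 12,600/0.90 = 14,000.
- The interval does not. At 40,000 per arm the counts are 30 and 40; SE(log RR) = sqrt(1/40 - 1/40,000 + 1/30 - 1/40,000) = 0.241; 95% CI = 1.333 × exp(±1.96 × 0.241) = 0.83 to 2.14.
- Reading 12,600 as tests in the two primary arms gives 12,600/0.30 = 42,000 visits per arm, 31.5 vs 42 diagnoses, CI 0.84 to 2.12.
- The stated limits imply SE = (ln 1.79 - ln 1.01)/3.92 = 0.146. That needs about 82 vs 109 diagnoses, i.e. about 109,000 visits per arm.

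**Denominator of the ICER, enhanced minus nontargeted.**
- 40,000 per arm: 40 - 30 = +10; SD = sqrt(40 × 0.999 + 30 × 0.99925) = 8.36; 95% CI = 10 ± 1.96 × 8.36 = -6.4 to +26.4.
- 14,000 tests all in the two primary arms (46,667 visits per arm): +11.7, 95% CI -6.0 to +29.4.

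**Simulated replicates at 40,000 per arm** (200,000 draws of tests and diagnoses): about 10% negative and 2% exactly zero. With equal yield (30 vs 30): about 47% negative and 5% zero.

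**Direction of cost.** Expected tests are 10,000 vs 2,000. Risk assessment applies to all 40,000 targeted visits, so enhanced targeting is cheaper only if its extra cost per visit is below (10,000 - 2,000)/40,000 = 0.20 of a test.

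**Ratio interval at 40,000 per arm**, in test-cost units per extra diagnosis:

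| Extra cost per visit (tests) | Point ICER | Percentile 95% interval | Replicates finding more | Replicates finding fewer |
|---|---|---|---|---|
| 0 | -800 | -7,880 to +4,038 | 87%, cheaper | 10%, cheaper |
| 0.10 | -400 | -3,872 to +2,034 | 87%, cheaper | 10%, cheaper |
| 0.25 | +200 | -1,032 to +1,874 | 87%, costlier | 10%, costlier |
| 0.30 | +400 | -2,026 to +3,858 | 87%, costlier | 10%, costlier |

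In the first two rows every positive value comes from replicates that are cheaper but find fewer cases, yet it reads as an ordinary price per extra case. In the last two rows every negative value is a dominated replicate, yet it reads as a saving.

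**Per-arm CERs.** Assume, for illustration, 40 dollars per test and 1 vs 3 dollars of nurse time per visit (extra cost 2/40 = 0.05 of a test). Nontargeted: (10,000 × 40 + 40,000 × 1)/30 = about 14,700 dollars, interval 10,700 to 22,100. Enhanced: (2,000 × 40 + 40,000 × 3)/40 = 5,000 dollars, interval 3,800 to 7,100. These denominators stay well away from zero. Under the same assumptions the ICER is (200,000 - 440,000)/10 = -24,000 dollars, with an interval of about -235,000 to +121,000.

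**The case against.** **Hypothesis 2 does not need the ICER.** It concerns cost per newly identified patient, which is each arm's CER, and both CERs are planned with intervals. This stands. A reader might infer that the planned output cannot settle Hypothesis 2; the Protocol does not support that. In the illustration above the CER intervals do not even overlap.

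**The Protocol does not place the result in the dominance quadrant.** This also stands. A reader might infer dominance from more diagnoses with one fifth of the tests, but no costs are given, and above 0.20 of a test per visit enhanced targeting is the costlier arm. The defect does not depend on this: about 10% of replicates cross zero effect in either case.

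**The stated RR interval of 1.01-1.79 excludes a zero difference.** It does as printed, so the straddle is not in the plan's stated figures. It appears on recalculating from the plan's rates and size. Even at the roughly 109,000 visits per arm which that interval needs, a dominant result (no extra screening cost) would give an interval of about -4,400 to -340 test units, and negative ICERs have no usable order.

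**Percentile limits are not specified, and details may sit in an analysis plan.** Fair as to the construction. But the Protocol itself commits to an interval for the ratio, and other bootstrap limits on the same replicates do not restore an order that the ratio lacks.

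**The ICER wording is loose.** "the additional costs per patient identified with HIV infection beyond those incurred by nontargeted screening" could be read as the difference between two CERs, which would avoid the problem. It is read here in the usual sense, difference in cost over difference in diagnoses, because the Protocol calls it an incremental cost-effectiveness ratio.

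**Section 4.H rules out decision analysis.** The fix needs no disease model; it only re-summarises the trial's own replicates.

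**Conclusion.** The concern holds for the ICER intervals and only for them. At the plan's own rates and maximum enrolment, the enhanced-versus-nontargeted denominator is +10 diagnoses with 95% CI -6.4 to +26.4. Some 12% of replicates are zero or negative if the planning assumptions are true, and about half if the pilot's equal yield recurs. An interval for the ratio would then be misleading whichever arm is cheaper.

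This rests on the section 4.I rates, 40,000 visits per arm (a maximum), independent visits, the conventional definition of the ICER and simple percentile limits. The widths in cost units also depend on assumed costs. No planning rates are given for the traditional arm, so the size of the problem for that ICER cannot be stated.

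**What to change.** In section 4.H, Specific Aim 2, keep the CERs with their bootstrap intervals and keep the bootstrap itself. Then:

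1. Define the ICER explicitly as difference in cost divided by difference in new diagnoses, each versus nontargeted screening.
2. Report incremental cost and incremental diagnoses separately, each with a 95% CI.
3. Plot the joint replicates on the cost-effectiveness plane and give the share in each quadrant.
4. State dominance in place of an ICER where it applies.
5. Give an ICER interval only when the replicates do not cross zero effect difference. Otherwise summarise uncertainty by incremental net benefit with 95% CI over a stated range of values per new diagnosis.

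This costs a few sentences of analysis text. The same replicates are used and no further data are needed. The downside is that more than one summary number is reported, and net benefit is shown over a range of values instead of as a single ratio.
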